### Sample size calculation

The primary outcome variable was fat mass loss after six months, and the anticipated minimum difference in the average fat mass loss was 2%, with an expected SD not exceeding 3.5% [35]. The study was designed to have at least an 80% power and an alpha level set at 0.5, obtaining a sample size of 27 individuals for each group (total *N* = 54). A total of 90 women (45 for each group), was estimated, to mitigate the effect of possible dropouts during this trial.

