### Eligibility criteria (inclusion and exclusion)

The women with the following pathologies or special situations was excluded from the study: Type 2 Diabetes, being or trying to become pregnant, being in a maternal lactation period, suffering from kidney failure, being under age, presenting a healthy weight (BMI ≤ 25) or receiving pharmacological antidepressant treatment. Women not possessing smartphones with Android or iOS operating systems and those without available data connections did not participate in the study.

Also, with the aim of homogenizing the study population, the inclusion criteria were: having a body fat percentage of ≥30%, being sedentary, defined as low energy sitting (or reclining) during waking hours [36], and not having been submitted to a restrictive diet in the 6 months prior to the beginning of the study. The flow chart of the participants is found in Fig. 1.

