#### Body composition

The percentage of body fat (BF), muscle mass (MM), and the percentage of water (W), considered to be result variables, were monitored and collected throughout the time by previously validated multifrequency bioelectrical impedance (BWB-800A, Tanita Corp. USA) [41]. This method is based on a 3-compartment model capable of evaluating BF, MM, and bone mineral content. Also, the percentage difference of each dependent variable was calculated throughout the weekly consultations, taking as a reference that recorded in the first one.

Likewise, the following independent variables were noted: age (years), height (cm), weight (Kg), and BMI (Kg/m2). The anthropometric measurements were taken following the recommendations in the standardized anthropometry handbook [42] by experienced personnel to diminish the coefficient of variation. Each measurement was taken three times, calculating the mean value. All the quantitative variables were measured with a precision of 0.1. For the height, a stadiometer (SECA 213) was used.

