### Statistical analysis

The quantitative variables were presented with the mean and the standard deviation, whereas the qualitative ones in frequencies and percentages. To contrast, the goodness of fit to a normal distribution of data from quantitative variables, the Kolmogorov-Smirnov test with the Lilliefors correction was used. For the bivariant hypothesis contrast, the two-means Student-t test was made, while, for the qualitative variables, the Chi-test and Fisher’s exact test was performed when necessary. Likewise, for the three or more means analysis, the ANOVA repeated means test was used to evaluate the effects of the intervention at the baseline moment, at 3 and 6 months, and the correlation between the quantitative variables was verified by Pearson’s (r) correlation coefficient. The ANCOVA analysis of covariance was applied to determine the effect of the baseline data on the modification of body composition. Finally, in the case of not fulfilling the criterion of normality or homoscedasticity, the non-parametric versions of the tests mentioned were conducted. Adjusted linear regressions were made for each variable of the body composition (%BF and MM) and the weight at the final moment of the study to estimate the standardized Beta coefficients possessed by the PUSH notifications in the achievement of objectives. For all the statistical analyses, an alpha error probability of under 5% (*p* < 0.05) was accepted, and the confidence interval calculated with a 95% security. For the statistical analysis, the computer program IBM SPSS Statistics version 22.0 will be used.

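### The ANCOVA is aimed at the effect of baseline on change in body composition; where both are the same variable, its baseline coefficient is not a valid answer and should not be interpreted

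*Protocol article*

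**What the plan says.** The Statistical analysis section gives the ANCOVA one purpose: "The ANCOVA analysis of covariance was applied to determine the effect of the baseline data on the modification of body composition". The effect of PUSH is estimated elsewhere in that section, by adjusted linear regressions on weight and body composition at the end of the study.

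The Body composition section says how change is measured: "the percentage difference of each dependent variable was calculated throughout the weekly consultations, taking as a reference that recorded in the first one". The variables concerned are percentage body fat, muscle mass and percentage water, which "were monitored and collected throughout the time by previously validated multifrequency bioelectrical impedance". The same section notes a second set of variables: "the following independent variables were noted: age (years), height (cm), weight (Kg), and BMI (Kg/m2"). It does not say which of these make up the baseline data in the ANCOVA.

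Two other statements matter for the size of the problem. The entry criteria include "having a body fat percentage of ≥30"%. The Sample size calculation section assumes a loss of fat "with an expected SD not exceeding 3.5"%.

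**The concern.** As worded, baseline is the effect to be determined, not an adjustment for a group comparison. If the response is change in body fat and the covariate is first-visit body fat, the first reading is both the predictor and the value subtracted. If change is relative, it is also the denominator.

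A woman whose first reading is too high by chance then appears both fatter at the start and more improved later. Dividing by the first reading creates a second link, in the opposite direction. Either can produce a significant baseline effect when true loss in points is unrelated to true baseline. At stake is a statement about which women benefit, whose direction could depend on the scale and on the error of the impedance device.

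**Working it through.** The plan gives no figure for this analysis, so there is none to reproduce. The check asks what the baseline coefficient estimates when true loss in points does not depend on true baseline.

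**Inputs from the protocol article**
- SD of loss 3.5, read as percentage points of body fat; group difference 2; total 90 women (Sample size calculation).
- Entry at a reading of 30% or more (Eligibility criteria).

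**Assumptions, not in the documents**
- Mean baseline body fat m = 38%; true SD 5 points (4 to 6 as a range).
- Mean loss 4 points (3 in control, 5 with PUSH).
- Measurement-error SD e from 0 to 2 points.
- The 3.5 may be the SD of observed change or of true change; both are shown.

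**1. Change in points.** The slope on the observed baseline is -e²/(e² + true SD²):
- e = 0.5: -0.25/25.25 = -0.01
- e = 1: -1/26 = -0.04
- e = 1.5: -2.25/27.25 = -0.08
- e = 2: -4/29 = -0.14

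**2. False rejection at a nominal 5%, worked for e = 2 and n = 90.**
- The observed baseline SD is √29 = 5.39. Cutting at 30 gives a = (30 - 38)/5.39 = -1.49, λ = φ(a)/(1 - Φ(a)) = 0.142, and SD = 5.39 × √(1 + aλ - λ²) = 4.72.
- With 3.5 as the SD of observed change: residual SD = √(12.25 - 0.138² × 29) = 3.42; SE = 3.42/(4.72 × √88) = 0.077; ratio 0.138/0.077 = 1.79; rejection about 43%. Simulation gives 41%.
- With 3.5 as the SD of true change: variance of observed change = 12.25 + 2 × 4 = 20.25; residual SD 4.44; SE 0.100; ratio 1.38; rejection about 28%. Simulation gives 28%.
- At e = 1 the same steps give about 7% and 8%; at e = 0.5, about 5%.
- Across true SDs of 4 to 6, simulated slopes run from about -0.03 to -0.06 at e = 1 (6-9% rejection) and from about -0.10 to -0.21 at e = 2 (20-66%).

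**3. The entry cut.** In simulation at true SD 5 and e = 2, the slope is about -0.136 with or without the 30% criterion. Rejection is lower with it: 44.3% against 50.7% at a mean of 40.

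**4. Relative change.** A uniform 4-point loss is 4/30 = 13.3% at baseline 30 but 4/45 = 8.9% at baseline 45. The slope with no error is about 100 × 4/38² = +0.28; simulation gives about +0.27, with 18-27% rejection. With error, the slope is approximately 100 × 4/m² - (100/m) × e²/(e² + 25):
- e = 1: 0.277 - 0.101 = +0.18
- e = 1.5: 0.277 - 0.217 = +0.06
- e = 2: 0.277 - 0.363 = -0.09

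The sign changes within the assumed range of error. Rejection with error is about 5-19%.

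**5. What is not affected.** With change in points, the adjusted PUSH coefficient averaged -1.98 to -2.03 against a true -2 in every setting. A covariate outside the outcome, such as age, kept its nominal size (4.3-5.3% rejection). A PUSH-by-baseline interaction on the six-month value averaged about 0 with about 5% rejection, because the artefact is the same in both randomised groups and cancels.

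**The case against.** The strongest reply is that the text does not fix this model. The baseline data are not listed. If they mean only age or height, nothing is shared between the two sides and the concern disappears. The statistics section also does not say that its response is the percentage difference of the Body composition section, and for body fat that phrase can mean percentage points. In a condensed article the sentence may loosely describe ordinary baseline adjustment, and none of the stated aims asks whether initial fat determines response. All of this stands as a limit. It does not remove the point: the only stated purpose is the effect of baseline, and for an ANCOVA of change the natural covariate is the baseline of the same variable.

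Second, the error SD is assumed. Triplicate means ("Each measurement was taken three times, calculating the mean value", stated with the anthropometry) and fasting measurement on the same weekday, at the same time and in the same clothes reduce error. They do not remove day-to-day variation, but they may bring it to a level where the point-scale bias is small.

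Third, the relative-scale slope depends on the null chosen. If true loss is proportional to baseline and there is no error, the relative slope is 0.00 (4.9% rejection) and the point slope is -0.11 (24.5%). Neither scale is wrong in itself; they answer different questions. That stands, and it is a reason to fix the scale before the coefficient is read.

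A reader might infer that selecting women on the same reading makes the bias worse. It does not: the cut leaves the slope unchanged and lowers the rejection rate. A reader might also infer that the PUSH result is compromised. The documents do not support that: PUSH is estimated separately on final values, and adjusting for baseline leaves the randomised comparison in points unbiased.

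**Conclusion.** The concern holds for the interpretation of one secondary coefficient, on the reading that covariate and response are the same body-composition variable. In points, with 90 women and a true SD of 5, the false slope is about -0.04 at 1-point error (7-8% rejection) and -0.14 at 2-point error (28-41%), and negligible at 0.5 points. On a relative scale, with uniform point loss, it is about +0.27 without error (18-27% rejection) and falls through zero as error grows. The baseline mean and SD, the mean loss and the error SD are all assumptions. It would go too far to say that the trial will report a false baseline effect: with small error and change in points, the test stays close to its nominal level. What can be said is that a significant coefficient, of either sign, could not be taken as evidence about who responds.

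**What to change.** In the Statistical analysis section, restate the ANCOVA as a comparison of the PUSH groups on the absolute six-month value, with the baseline value of the same variable as an adjustment term whose coefficient is not interpreted. Name the baseline covariates. Do not use the percentage difference from the first visit as the response in this model.

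Only if the sponsor wants to know whether baseline modifies the PUSH effect, add a PUSH-by-baseline interaction to that model, report it with a 95% confidence interval and label it exploratory.

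The cost is a change of wording and, if wanted, one model term; no new data are needed. The drawback of the interaction is that it is imprecise with 90 women. It also remains specific to the scale of the response.

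### A normality or equal-variance check decides whether unnamed non-parametric tests replace the planned mean-based tests, so method and effect measure depend on the data, and unequal variances are not remedied

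*Protocol article*

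**What the plan says.** The Statistical analysis section of the protocol article sets out the following, in this order.

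- Normality of the quantitative variables: "the Kolmogorov-Smirnov test with the Lilliefors correction was used".
- Two-group comparison: "the two-means Student-t test was made".
- Repeated measurements: "the ANOVA repeated means test was used to evaluate the effects of the intervention at the baseline moment, at 3 and 6 months".
- Baseline: "The ANCOVA analysis of covariance was applied to determine the effect of the baseline data on the modification of body composition".
- The switch: "in the case of not fulfilling the criterion of normality or homoscedasticity, the non-parametric versions of the tests mentioned were conducted".
- After the switch: "Adjusted linear regressions were made for each variable of the body composition (%BF and MM) and the weight at the final moment of the study". Their purpose is to gauge the contribution of the PUSH notifications.

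The section names neither a test for equal variances nor the non-parametric replacements or their effect measure. The Sample size calculation section says: "The primary outcome variable was fat mass loss after six months". It plans on a 2% difference in average loss with an SD of at most 3.5%, and on enrolling 45 women per group.

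**The concern.** The trial is sized for a difference in means. Under the rule, that difference is tested only if the data pass a preliminary check. Otherwise an unnamed rank-based procedure takes over. It answers a different question and gives no estimate in percentage points of fat. Method and effect measure could then differ between outcomes and visits, and would be known only after the data are seen.

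The rule also treats failed equal variance as a reason to use a rank test. That test is itself sensitive to unequal spread, so the trigger and the remedy do not match.

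Finally, ANCOVA is among the tests mentioned before the switch. The usual rank tests (Mann-Whitney, Kruskal-Wallis, Friedman) take no covariate, so baseline adjustment may be lost there.

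**Working it through.** **Inputs.** From the Sample size calculation section: difference 2, SD of loss 3.5, 45 per group enrolled, 27 per group before allowance for dropout. From the Statistical analysis section: 5% level. Assumed, because the article does not give them: two-sided tests, Levene as the variance test, SD ratios, distribution shapes and the baseline/follow-up correlation.

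**The plan's own figure.** The plan attaches no number to the switching rule. Its sample size does not reproduce as a two-group calculation: 2 × (1.960 + 0.842)² × 3.5² / 2² = 48.1, or 49 per group, against the stated 27. That is a separate matter, and nothing below depends on it.

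**1. How often the switch fires when nothing is wrong.** With normal, equal-variance data, Lilliefors in two independent arms gives 1 − 0.95² = 9.75%. Treating Levene as a third independent check gives 1 − 0.95³ = 14.3%. Simulation at 45 per arm gave 9.7% for Lilliefors in either arm, 4.6% for Levene, and about 13-14% for any of them.

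**2. Whether the replacement tests the planned quantity.** One arm was exponential and the other normal, with equal means and equal SDs, so the mean difference is zero. At 45 per arm the rank-sum test rejected in 9.5% of trials and the t-test in about 5% (4.7% to 5.1% across runs). At 27 per arm the figures were 8.0% and 5.6%. The rank-sum test is responding to shape, not to the mean difference.

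**3. Whether the replacement cures unequal variances.** Normal data, equal means, SDs 3.5 and 7, nominal 5%:

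| n with SD 3.5 / n with SD 7 | Student t | Rank-sum | Welch |
|---|---|---|---|
| 45 / 45 | 4.9% | 5.7% | 4.8% |
| 45 / 27 | 9.6% | 7.4-8.1% | 4.6-5.2% |
| 27 / 45 | 2.3% | 3.7% | 5.1% |

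With equal arms the rank-sum inflation is 5.7 − 5.0 = 0.7 points; at an SD ratio of 3 it reaches 6.8%. With unequal arms the rank-sum test improves on Student's t but does not restore the level, whereas Welch does. The 45/27 split is severe: one arm loses 18/45 = 40% and the other loses nobody.

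**4. What the switch costs overall.** For normal change scores at 45 per arm, the full two-stage procedure had type I error of 4.8-4.9% and power of 76.4-76.6%, against 76.7-76.8% power for the t-test alone. By formula, the t-test's power is Φ(2 / (3.5 × √(2/45)) − 1.96) = Φ(2.71 − 1.96) = 77%.

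**5. What a fixed, baseline-adjusted model gives.** Let ρ be the baseline/follow-up correlation. If the SD of change is 3.5, the ANCOVA residual SD is 3.5 × √((1 + ρ)/2).

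- ρ = 0.5: 3.5 × 0.866 = 3.03. Power is Φ(2 / (3.03 × 0.211) − 1.96) ≈ 88% (simulated 87%).
- ρ = 0.8: 3.5 × 0.949 = 3.32. Power is Φ(2 / (3.32 × 0.211) − 1.96) ≈ 82% (simulated 79-81%).

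The gain over 77% comes from using the baseline value, not from avoiding ranks.

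**The case against.** The strongest reply is that this is a generic good-practice point with little practical effect, and much of that reply stands.

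- **Power.** A reader might infer that power falls whenever the switch fires. The calculations do not support this. With normal data the two-stage procedure matches the t-test. With exponential change in both arms, where the rule almost always fires, power rises from about 77% for the t-test to about 96% for the rank test, with type I error of 4.6%.
- **Baseline adjustment.** A reader might infer that the rule removes it altogether. The text does not say so. The planned t-test was already unadjusted, rank-based forms of ANCOVA exist, and the adjusted regressions come after the switch sentence and are not expressly covered by it. The ANCOVA is also described as examining the effect of baseline data, not clearly as the treatment comparison.
- **Eligibility cut.** Entry requires "having a body fat percentage of ≥30" per cent, and a reader might infer that this truncation makes the switch likely to fire. The cut acts on baseline values, whereas the primary outcome is loss. With assumed truncated baselines (mean 34-38, SD 5, correlation 0.5 or 0.8), Lilliefors rejected the change scores in 4.5-5.4% of samples, which is the nominal rate.
- **Condensed article.** A fuller protocol or analysis plan may name the replacement tests and say what is checked. So the missing names are not themselves the fault.

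What remains is the rule the article does state. It makes the method depend on the data, and it prescribes rank tests for unequal variances, which they do not cure.

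**Conclusion.** The point holds, at low severity. The method and effect measure of the comparison depend on a preliminary check and can leave the mean-difference scale on which the trial was sized. The remedy prescribed for unequal variances does not work. It leaves type I error at about 7-8%, against about 5% for Welch, when the smaller arm has twice the SD at 45 and 27 women. With equal arms and the same SD ratio the inflation is under 1 point. Loss of baseline adjustment is possible where ANCOVA would switch, but it is not established.

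These sizes rest on assumed SD ratios, arm sizes and shapes, and on Levene as the variance check. The article supplies only the difference, the SD and the planned numbers. The main reason to act is that the change is cheap and makes better use of a baseline value that is collected anyway.

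**What to change.** For the primary comparison, delete the switching rule. Pre-specify a linear model (ANCOVA) for six-month body fat on randomised PUSH group and baseline body fat, with heteroscedasticity-robust standard errors, to be used whatever the normality tests show. Adjusting for baseline gives the same group coefficient whether the response is the final value or the change, so the result stays on the planned mean-difference scale. Check residuals graphically, and report a rank-based or bootstrap analysis as a sensitivity analysis only.

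The cost is analysis wording, with no extra women, visits or measurements. The Abstract describes message delivery as in progress and the Data Availability statement reports no datasets analysed, so on the article's own account the wording could be settled before analysis. Under the normal-data assumptions above, power at 45 per group moves from about 77% to about 80-87%.

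There is one small downside. With strongly skewed changes a mean-based analysis can be less powerful than a rank test (about 77% against 96% for exponential data). The sensitivity analysis would show this.

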## Discussion

The general objective of this protocol was to evaluate (1) the efficacy of PUSH notifications in an intervention aimed at improving the body composition of adult women who are overweight or obese, through dietary intervention, (2) analyzed the evolution of body composition based on PUSH notifications and prescribed physical activity. The intervention was evaluated through a randomized three-armed clinical test. It has been seen in the literature that the results of actions using mobile messaging via Push notifications could improve the degree of adherence to dietary prescriptions and physical activity, with different results. A significant number of women present physical activity levels below the minimum threshold recommend by official organizations. This sedentary lifestyle causes gains in total body weight and body fat. If the results of the assay demonstrate a positive effect, a new approach will be established based on the interaction of an APP and personal consultation, helping health professionals to establish real objectives in the prescription of physical activity and its follow-up in the patients who carry them out.

## Data Availability

Data sharing is not applicable to this article as no datasets were generated or analysed during the current protocol.

## Abbreviations

APP: Applications
BF: Body fat
BMI: Body mass index
IPA: Intense physical activity
LPA: Light physical activity
MM: Muscle mass
MPA: Moderate physical activity
PA: Physical activity
W: Water
